### Sample size

Based on the crossover design, we calculated that 120 participants with PPA (40 at each of the three sites) are needed to achieve 85% power in detecting the target effect size (e.s.^target^). The power of the design to detect e.s.^target^ using an estimator is calculated as/is Φ(*e.s*_*target*_/√(*rate*_*design*_/*n*) - 1.96), where *rate*_*design*_/*n* represents the standard error squared of the estimator, and Φ is the cumulative distribution of the normal. Plausible values of *rate*_*design*_ and effect sizes are determined based on similar outcomes from previous studies with comparable crossover designs. The estimated 15% dropout rate is based on previous studies involving individuals with PPA undergoing tDCS and language therapy. In prior RCT from members of our team, attrition was ~15% during the first phase, mostly due to unrelated medical issues (Tsapkini et al., 2018). This rate was used to estimate the required sample size.

### Selection and treatment of participants

This study population will consist of 120 individuals diagnosed with lvPPA or nfvPPA by their neurologist, based on a comprehensive neurologic evaluation, with the diagnosis confirmed through neuroimaging. Based on previous research carried out by team members (Tsapkini et al., 2018), it was decided not to include individuals with svPPA because although they showed learning effects for trained items, the effects did not generalize to untrained items or tasks. Thus, this study aims to determine the adjuvant effect of tDCS in 2 populations of individuals living with PPA that responded to a similar type of therapy in our previously published studies.

Recruitment will also include 60 healthy controls matched with participants for age and education across all sites. These controls will participate in one MRI scan and one clinical, cognitive, and language assessment to evaluate the normal variability of the measures included in the trial and whether tDCS can normalize participants' neural response patterns.

### Randomization and blinding

As shown in Table 1, following the T1 assessment, participants will be randomly allocated to either Group 1 or Group 2, thereby determining the order of stimulation conditions. Randomization is performed independently for each variant (lvPPA and nfvPPA), employing block randomization with blocks of four participants, and each site performs randomization independently. Within each block, two individuals will be assigned to Group 1 and the other two to Group 2, ensuring balanced allocation across treatment arms within each PPA variant. Randomization ensures a balanced allocation of treatment sequences across participants, thereby controlling for potential order effects and minimizing biases associated with the crossover design (such as period effects and potential carry-over effects, although limited in this study by the washout period of 3 months (Li et al., 2015; Piantadosi, 2024).

Following the allocation, each participant will be assigned 15 unique five-digit codes provided by the manufacturer of the tDCS stimulator upon device programming (one for each intervention day), indicating whether they receive active stimulation (a-tDCS) or placebo (s-tDCS). The codes are necessary to initiate the tDCS delivery device, but do not reveal whether active or sham stimulation is administered. The research team (including therapists and assessors) and participants will be blinded to whether a- or s-tDCS is being administered during each period to maintain a fully blinded study design. The code list will be decrypted upon study completion to identify when each participant received a- and s-tDCS. The specific programming of the tDCS device during the s-tDCS period condition can be found in the tDCS section below.

### Inclusion and exclusion criteria

#### Inclusion criteria

We will include 120 participants with PPA who are between 50 and 80 years of age, right-handed, proficient in English, and have a minimum of a high school education. Participants must be diagnosed from a PPA and Alzheimer's disease (AD) clinics at the University of Pennsylvania, Johns Hopkins University, the University of Toronto, or other specialized referral centers in the US and Canada, using current consensus criteria (Gorno-Tempini et al., 2011). To corroborate the diagnosis, AD biomarkers (CSF or PET amyloid β I-42) will be examined and we will use our variant classification tests developed, including a spelling task and a speech production task (Cookie Theft picture description task (Goodglass and Kaplan, 1983), which can accurately discriminate PPA participants with over 80% accuracy (Themistocleous et al., 2021; Neophytou et al., 2019).

Participants are asked to maintain their daily habits as consistently as possible throughout the trial. Therefore, individuals already receiving speech-language therapy before enrolling in the project may continue to see their therapist. However, participants who were not already seeing a therapist are requested to wait until the end of the trial before starting any new therapy sessions.

#### Exclusion criteria

We will exclude individuals who have any of the following: a history of neurological disease, including vascular dementia, large vessel stroke, or attentional deficit; uncorrected hearing loss or visual acuity loss; a history of major pre-morbid psychiatric disorders; left-handedness; or advanced dementia impairments [Mini-Mental State Examination (MMSE) (Folstein et al., 1975) < 15] or severe language impairments preventing the participation in assessments and therapy.

### Interventional methods

#### NaSp therapy

In this trial, the overarching aim of the intervention is to enhance communication effectiveness in individuals living with PPA by improving their spoken naming and spelling of nouns and verbs. NaSp was developed based on our previous work (Tsapkini et al., 2014, 2018), and improved based on additional evidence from the literature to enhance spoken naming specifically (Rapp and Glucroft, 2009; Tsapkini and Hillis, 2013; Beeson et al., 2002). While NaSp includes elements from these earlier therapies, it also incorporates modifications that target spoken naming abilities—an aspect not effectively addressed by the therapy used in our prior studies.

Using the Rehabilitation Treatment Specification System (Hart et al., 2019) as a framework, NaSp can be described as a multi-stage intervention that is decomposable into *therapy targets*, each of which is linked to specific *active ingredients*. Specific *Skills and Habits* targets include improving spoken naming and spelling accuracy of trained and untrained nouns and verbs, increasing metacognitive skills to compensate for anomia, and enhancing language and cognitive skills to support communication. An *Organ Functions* target is to improve the efficiency of the language network in the brain in the presence of neurodegeneration. Finally, *Representation* targets are to increase confidence in communication and maximize engagement and collaboration. While breaking NaSp down into its specific active ingredients provides a detailed therapeutic perspective, it goes beyond the scope of this paper and will be addressed in a subsequent publication.

During NaSp therapy sessions, each trial consists of two phases –spoken naming and spelling. Figure 2 illustrates the flow of NaSp therapy. Each trial begins with the spoken naming phase, in which individuals with PPA are presented with a picture and asked to name it orally. If successful, they proceed to write the word. If unsuccessful, they receive prompts to generate three semantic cues to aid in naming, followed by a phonemic cue if needed. During the cueing, participants are encouraged to name the picture as early as they can (i.e., they do not need to wait for the three semantic cues). If the participant can still not name the picture, the spoken word is provided, and they are asked to repeat it three times before moving on to spelling. In the spelling phase, participants are asked to write the word corresponding to the picture. Successful attempts are reinforced by confirming the provided answer is correct, while unsuccessful attempts prompt PGC training–also known as sound-to-letter correspondence–for the target word being trained (Tsapkini and Hillis, 2013). Following the PGC training, participants must attempt to write the word corresponding to the picture a second time, with reinforcement provided upon successful completion. If unsuccessful, they are guided through the writing process: the speech-language therapist (or a trained research assistant), hereafter referred to as the therapist, shows the word again and provides PGC training while the participant copies it. In cases where participants improve substantially within the first sessions of intervention, the therapist encourages the participant to form sentences using the target words or engage in personally relevant conversations about the target word to ensure all participants receive at least 45 min of therapy.

**Figure 2 F2:**
[figure not shown]
The flow of NaSp therapy.

As shown in Table 1, Figure 1, a therapist will administer therapy 5 days per week for three consecutive weeks. Therapy will last between 45 and 90 min, including the concomitant stimulation during the first 20 min. The exact duration of therapy will vary depending on the participant's tolerance for effort and speed of execution, and breaks will be taken if needed. Therapy will be conducted individually, in person, in a quiet room.

During each therapy session, the 20 words on the trained list (described in the next section) will be used for that period. To ensure therapy validity across different sites, a NaSp app was developed by the first author ([name]) in R using Shiny App. The app guides the therapist in following the NaSp flow according to the participant's answers. It allows the therapist to track the participant's spoken and written naming performance, as well as the effectiveness of cues when used. A comprehensive NaSp tutorial was also developed to help train therapists at the different sites.

##### Therapy stimuli

Two sets of therapy stimuli were developed for NaSp, targeting two levels of baseline performance. This structure reflects the clinical reality of variability in naming performance among individuals with PPA. It is guided by psycholinguistic evidence showing that lexical characteristics such as word frequency, length, imageability, and age of acquisition influence naming success (Vonk et al., 2019; Jebahi et al., 2023). This two-level approach offers a scalable and principled method for adapting therapy difficulty to participant ability, all while maintaining methodological consistency and control over psycholinguistic variables. Level 1 (easier words suitable for more moderate or advanced difficulties based on naming performance on the Level I list at the T1 assessment, < 70% correct) and Level 2 lists (more challenging words suitable for milder impairments based on naming performance on the Level 1 list at the T1 assessment, 70% or greater correct). Each level consists of 80 stimuli, comprising both nouns and verbs, and levels differ in psycholinguistic factors, based on the English Lexicon Project (Balota et al., 2007).

In Level 1, therapy words are characterized by shorter lengths [mean (*M*) ± standard deviation (*SD*)] 5.33 ± 1.23 letters for nouns and 5.63 ± 1.53 letters for verbs, higher frequency (21.20 ± 17.41 for nouns and 13.20 ± 21.29 for verbs), and an earlier age of acquisition (AoA; 5.15 ± 1.21 for nouns and 6.41 ± 1.68 for verbs). All words in this level are imageable, and corresponding pictures were sourced from the International Picture Naming Project (Székely et al., 2003; Szekely et al., 2005). Level 1 consists of a total of 40 nouns and 40 verbs.

Level 2 stimuli are longer (9.06 ± 1.02 letters for nouns and 9.31 ± 1.01 letters for verbs), of lower frequency (1.25± 1.29 for nouns and 0.75 ± 0.86 for verbs), and a later AoA (11.63 ± 2.25 for nouns and 11.07 ± 2.57 for verbs). Because not all words in this level are imageable, short definitions were crafted for all therapy stimuli to be read jointly with the presentation of the picture. Pictures for Level 2 were obtained from both the International Picture Naming Project (Székely et al., 2003; Szekely et al., 2005) and The Noun Project (2023). This level consists of 64 nouns and 16 verbs.^3^

Following the T1 assessment, the therapy level for each participant is determined based on their performance, and they remain at that level for all subsequent study periods. For each participant, four random lists are generated, each containing 20 items designated for treatment in Period 1, 20 for generalization measurement in Period 1, 20 for treatment in Period 2, and 20 for generalization measurement in Period 2. All lists are matched for the above-specified psycholinguistic factors, including AoA, frequency, and word length. Participants assigned to Level 2 are also probed on items from Level 1 at each assessment to help track general decline throughout the trial.

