### Objectives

This paper reports the protocol and analysis plan for the clinical trial NCT05386394, registered on http://clinicaltrials.gov, which implements a multisite, randomized, double-blind, sham-controlled, within-subject crossover design. The trial aims to assess the effectiveness of a-tDCS targeting the left IFG combined with a novel, theoretically driven behavioral naming treatment in improving spoken naming and spelling abilities in individuals with lvPPA or nfvPPA. The overall goal is to bring tDCS combined with spoken naming and spelling therapy from the research lab closer to the clinic. We hypothesize that a-tDCS targeting the left IFG concurrent with spoken naming and spelling therapy will yield superior improvements compared to sham-tDCS (s-tDCS) paired with the same behavioral therapy, with sustained effects for up to 3 months post-treatment and generalization to untrained items as well as broader language and cognitive tasks subserved by the same area of stimulation. Additionally, we aim to evaluate factors already identified as potential predictors of treatment response, including PPA subtype, aphasia severity, cortical and neurofunctional measures, cognitive abilities, genetic markers, lifelong language experience, and demographic variables such as age and sex.

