#### Primary outcome measures

The primary outcome measure will be the change in performance between time points, as measured by phonemic accuracy (during spoken naming) and letter accuracy (during spelling) of trained items. Phonemic and letter accuracy will be calculated on a scale of 0–100%, with a higher number reflecting higher accuracy, using the Phonology analysis and Spelling analysis tools in Open Brain AI (Themistocleous, 2023).

At each assessment time point, participants undergo a comprehensive evaluation that includes the NaSp spoken naming and spelling task, which serves as the primary outcome measure. The task consists of 80 stimuli corresponding to the Level 1 stimuli previously outlined in the Therapy Stimuli section (along with 80 items included in Level 2 for identified participants). Accuracy on trained items is then computed separately.

The assessor presents all the words in the list. For each noun, participants attempt to name the item orally and then write their answer. No feedback is given, as some items serve as generalization items for either P1 or P2. After assessing the nouns, the same procedure is applied to the verbs.

All spoken and written responses are recorded. Spoken responses will be transcribed manually using the International Phonetic Alphabet, and written responses are captured using a smart pen (Symphony Smartpen by Livescribe, n.d.) to ensure accurate data collection. Both the spoken and written responses will be typed into a scoring document.

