#### Secondary outcome measures

The secondary outcome measures will be the changes in performance between time points, specifically phonemic accuracy (during spoken naming) and letter accuracy (during spelling) of untrained items. Similar to the primary outcome measure, phonemic and letter accuracy will be calculated on a scale of 0–100%, with higher numbers indicating greater accuracy, using the Phonology analysis and Spelling analysis tools in Open Brain AI (Themistocleous, 2023). The performance on the NaSp spoken naming and spelling task will be used to compute the accuracy of the untrained items.

Additionally, resting-state functional MRI (rs-fMRI) will be used to measure the activity of various brain regions during resting or task-negative conditions. This approach will allow for the evaluation of functional interactions between brain regions. Further details regarding the neuroimaging methods are provided below.

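### Generalisation is scored on a different 20 of the 40 never-trained items in each period; scoring the same 40 in both would gain precision at no testing cost

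*Protocol article*

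**What the plan says.** - **Lists.** Under Therapy stimuli, "Each level consists of 80 stimuli, comprising both nouns and verbs". Each participant's 80 items are divided at random into four lists of 20, matched on age of acquisition, frequency and word length. One is the training list of the first period; the other three are given as "20 for generalization measurement in Period 1, 20 for treatment in Period 2, and 20 for generalization measurement in Period 2".
- **Therapy.** Only the current period's training list is used (NaSp therapy): "During each therapy session, the 20 words on the trained list (described in the next section) will be used for that period".
- **Testing.** Under Primary outcome measures, "At each assessment time point, participants undergo a comprehensive evaluation that includes the NaSp spoken naming and spelling task", and "The assessor presents all the words in the list". The same section repeats the link between list and period: "No feedback is given, as some items serve as generalization items for either P1 or P2". Data collection sets seven assessments, with T4 serving both as the 3-month visit of Period 1 and as the baseline of Period 2.
- **Outcome.** Under Secondary outcome measures the outcome is change in accuracy on untrained items: "The performance on the NaSp spoken naming and spelling task will be used to compute the accuracy of the untrained items". That section does not say which untrained items count in which period.
- **Hypothesis.** Under Objectives, active stimulation is expected to be superior "with sustained effects for up to 3 months post-treatment and generalization to untrained items".

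**The concern.** For trained words, each period must have its own list, because a word trained in Period 1 is no longer a fresh target in Period 2. That reason does not extend to the generalisation lists. Neither is ever trained and both are tested on the same occasions. At T4 the Period 2 list is therefore no fresher than the Period 1 list, and any practice effect or generalised effect of Period 1 has had the same opportunity to reach both.

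With period-specific scoring, each period uses 20 of the 40 available items, and active and sham are compared within a person on different words. What is at stake is precision on the main behavioural secondary outcome, which carries the generalisation hypothesis. Generalisation also matters to the design: its absence in the semantic variant is the reason given for excluding that group.

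**Working it through.** **The plan's own figure.** Sample size gives 120 participants for 85% power. The target effect and the design variance rate have no stated values, so the figure cannot be reproduced. Back-solving gives only their ratio, effect/√rate = (1.96 + 1.036)/√120 = 0.2735. The number of items does not appear in the calculation.

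**Item count.** 80 − 20 − 20 = 40 never-trained items, of which 20 are assigned to each period.

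**Item-noise variance of the within-person active-minus-sham contrast.** Let s² be the variance of one item's score at one visit, independent across items and visits.

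- Immediate contrast, (T2 − T1) − (T5 − T4), up to sign:
  - separate lists: 2s²/20 + 2s²/20 = 0.20 s²
  - same 40 items: 4s²/40 = 0.10 s², which is 50% less
- 3-month contrast, (T4 − T1) − (T7 − T4) = 2·T4 − T1 − T7:
  - separate lists: the T4 values come from different items, so again 0.20 s²
  - same 40 items: (4 + 1 + 1)s²/40 = 0.15 s², which is 25% less

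**Without the independence assumption.** Let v be the variance of an item's change, equal in the two periods, and r the correlation between an item's two period changes. Separate lists give 2v/20 = 0.10v. The same 40 items give 2v(1 − r)/40 = 0.05v(1 − r), which reaches 0.10v only at r = −1. Pooling therefore cannot do worse. The results above are the cases v = 2s² with r = 0 and r = −0.5.

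**Total variance.** Add a between-person contrast variance τ², which the choice of items does not change. The documents give neither s² nor τ. The assumed ranges are s² = 0.05 to 0.25 on the 0–1 scale (0.25 is the largest variance possible on that scale) and τ = 5 to 20 points.

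| s² | τ (points) | Immediate: pooled/split | 3 months: pooled/split |
|---|---|---|---|
| 0.05 | 5 | 0.0075/0.0125 = 0.60 | 0.0100/0.0125 = 0.80 |
| 0.05 | 20 | 0.045/0.050 = 0.90 | 0.0475/0.050 = 0.95 |
| 0.25 | 5 | 0.0275/0.0525 = 0.52 | 0.0400/0.0525 = 0.76 |
| 0.25 | 20 | 0.065/0.090 = 0.72 | 0.0775/0.090 = 0.86 |

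**What this means for power.** Take an effect that would have 85% power with separate lists. With pooled lists its power is Φ(2.996/√ratio − 1.96). That is 0.885 to 0.985 for ratios of 0.90 to 0.52, and 0.867 to 0.930 for ratios of 0.95 to 0.76. The plan does not state power for this outcome, so 85% is only a reference level.

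**Carryover.** Equal histories imply equal carryover in the two lists. A simulation built on that premise, with a true effect of 5 points and a carryover of 3 points, returned about 6.5 points under either scoring rule. The bias is half the carryover (3/2 = 1.5 points), and the choice of list neither adds to it nor removes it.

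**The case against.** Much of the case for leaving the plan alone is sound.

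- **The outcome section does not fix the rule.** It says only untrained items, and a condensed article may leave the scoring detail to a fuller document. This stands in part. The only assignment the article gives is the period-specific one, stated under Therapy stimuli and repeated under Primary outcome measures. Read alone, the outcome section would allow 20, 40 or even 60 items in Period 1, since the Period 2 training list is still untrained then.
- **There is no bias.** A reader might infer that comparing different words distorts the contrast. The documents do not support that. The outcome is change from baseline on the same list, so additive differences in list difficulty already cancel. Lists are drawn at random and matched for each participant, and treatment order is randomised. Only list-to-list differences in headroom or responsiveness remain, and these act as noise.
- **No data are thrown away.** A reader might infer that half the never-trained items are lost. All 40 are collected at every assessment and each list is used once, so the matter is one of scoring.
- **The split is not offered as protection from carryover.** Statistical analysis relies on an interaction term, a Period 1-only sensitivity analysis and a washout check. That the split gives no such protection is therefore not an error in the plan.
- **The gain is modest in absolute terms.** At an assumed s of 30 points the per-participant item-noise SD is 13.4 points with separate lists, against 9.5 (immediate) or 11.6 (3 months) with pooled lists. Divided by √120, these contribute about 1.2, 0.9 and 1.1 points to the standard error, before between-person variation is added.
- **Separate lists have some merit.** They keep T4 item noise from entering both 3-month changes, and they give trained and untrained scores the same number of items. The first is why the 3-month gain is 25% and not 50%, but pooling still comes out ahead. The second is tidy but not needed, since trained and untrained accuracy are separate outcomes.

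**Conclusion.** The point holds as a cheap improvement, not as an error or a threat to validity. Scoring a different 20 of the 40 never-trained items in each period gives up precision on the untrained-item secondary outcome for no matching benefit. The 50% and 25% reductions apply to item noise only and rest on noise being independent across visits. That pooling cannot do worse needs only equal change variance in the two periods. The effect on total variance depends on quantities the document does not give: over the assumed ranges it falls by 10 to 48% immediately after therapy and by 5 to 24% at 3 months. A further small gain is that differences in headroom or responsiveness between the two lists drop out of the contrast.

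**What to change.** State under Secondary outcome measures that in both periods the outcome is accuracy on the same 40 never-trained items at the participant's assigned level, pooling the two generalisation lists. Period 1 change runs from T1 to T2 and T4, and Period 2 change from T4 to T5 and T7. Keep the period-specific 20-item score as a sensitivity analysis, and settle the wording before the stimulation codes are decrypted.

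The cost is one sentence and a change to the scoring program. No extra testing is needed, because every item is already administered at every assessment. The small downside is that the two 3-month changes then share the T4 score on the same items; the planned within-person robust variance handles this, and the 25% figure already includes it.
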